#### Psychological Parameters

HRQOL will be assessed using the validated Kidscreen and validated Pediatric Quality of Life Inventory (PedsQL) questionnaires. The 23-item PedsQL addresses the multidimensional scales of physical, emotional, social, and school functioning. The questionnaire consists of five options ranging from “never” to “almost always” [42]. Additionally, the 27-items Kidscreen will be used to measure HRQOL for five dimensions (physical well-being, psychological well-being, autonomy & parent relation, peers & social support, and school environment) [43].

Motivation toward PA will be measured using the self-administered validated Behavioral Regulation in Exercise Questionnaire-2 (BREQ2). The BREQ2 consists of 19 questions with a 5-point scale, which measures different aspects of motivation (external regulation, identification, introjection, integration, motivation, and intrinsic regulation) and has been shown to have good factorial validity [44].

#### Parenting Questionnaires

Parents will be asked to fill in an online questionnaire regarding family composition, country of birth, educational level, and self-reported height/weight. In addition, parents will be asked to fill in the validated 85-item comprehensive general parenting questionnaire (CGPQ). The CGPQ assesses the following five key parenting constructs that have been identified across multiple theoretical approaches of parenting: “nurturance,” “structure,” “behavioral control,” “coercive control,” and “overprotection” on a five-factor scale [45].

The parent version of the validated Kidsscreen-27 questionnaire will be used to determine a HRQOL score of the child, and it consists of 27 questions. These questions are similar to the Kidsscreen-27 child version [43].

#### Feasibility

To understand which components of the intervention are successful, feasibility of the BOOSTH intervention will be assessed using a mixed-methods design including semistructured focus groups with teachers and evaluation questionnaires. In addition, the strengths, limitations, opportunities, and recommendations for future development will be asked.

Semistructured focus group interviews will be performed with teachers from the intervention schools. Prefixed interview guides will be used, with the possibility of additional follow-up questions, which allows the researcher to cover both contextual factors and intervention implementation. Questions will be asked about the introduction lesson of BOOSTH, the implementation and stimulation of BOOSTH by the teachers, and suggestions for future development of BOOSTH.

Children and their parents will be asked to fill in an evaluation questionnaire about their experiences with BOOSTH. Teachers will be asked to fill in an evaluation questionnaire about the implementation of the BOOSTH intervention.

#### BOOSTH Step Count

Children who are allocated to the intervention schools will receive the BOOSTH activity tracker. The BOOSTH activity monitor is a lightweight triaxial accelerometer–based activity monitor, which is worn around the wrist and measures the step count. Moreover, the BOOSTH activity monitor resets automatically at midnight and stores data of the previous day automatically on the device. Data are stored on the device for 30 days. A child or parent has to synchronize the BOOSTH activity monitor with a smartphone or tablet to retrieve the measured step count. The BOOSTH activity tracker will be used as a motivation tool to promote PA. The step count on the BOOSTH activity tracker will not be used for research purposes.

### Statistical Analysis Plan

Numerical variables will be presented as mean and SD or median and IQR where appropriate. Categorical data will be presented as number and percentage of participants in each of the possible categories. Baseline characteristics will be analyzed for differences between the groups, using independent sample *t* tests or Mann-Whitney *U* tests for numerical variables and chi-square or Fisher exact tests for categorical variables. The effects of BOOSTH on numerical outcome parameters (such as MVPA, cardiovascular parameter, and HRQOL) will be analyzed using linear mixed models in order to correct for dependent observations owing to repeated measurements within a child and clustering of children within a school. Stratification variables and relevant variables related to the outcomes (such as BMI [z-score], sex, age, and parenting style [measured with the CGPQ]) and/or missingness will be taken into account. A random intercept on school level and an unstructured covariance structure for repeated measures will be included. A *P* value <.05 will be considered statistically significant. All analyses will be performed using IBM SPSS Statistics for Windows version 25.0 (IBM Corp).

The feasibility of the study will be investigated using a mixed-methods design. Qualitative data of the focus group interviews will be audio recorded and transcribed verbatim. Interview transcripts will be coded by themes and concepts using NVivo version 12 software (QSR International). Coding will be performed by two researchers.

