## Methods

### Recruitment and Participants

The BOOSTH study is a cluster randomized controlled trial at 16 primary schools located in the province of Limburg (the Netherlands). Schools will be randomized to standard physical education curriculum plus BOOSTH (intervention schools) or standard physical education curriculum only (control schools). Stratified randomization will be applied by an independent researcher. Stratification variables are community (ie, schools need to be located within the same community) and school size (ie, number of children in a school). Control schools will only be visited for physical measurements. The inclusion criteria for the children are as follows: boys and girls in classes five to seven (age range 7-12 years) at the moment of inclusion and written informed consent from both parents and children older than 12 years. Children will be excluded if they are wheelchair dependent.

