### Sample Size Requirements

The sample size calculation is based on the primary outcome as follows: to detect a difference in MVPA between the intervention and control groups after 12 months. Children are nested within schools, with eight intervention and eight control schools.

Children from grades five till seven (age range 7-12 years) will be included in this study. Based on the participation rates of other Dutch school-based PA interventions, it is expected that about 60 children per school will participate. Therefore, 480 children per condition (intervention/control) (8×60=480) will be included. It is assumed that the intraclass correlation coefficient is between 0.05 and 0.10 [25]. When an intraclass correlation coefficient of 0.10 is used, the design effect (accounting for clustering of 60 children within a school) is equal to 6.9 (1+[60−1]×0.10). Accounting for a dropout rate of 20%, the effective sample size (sample size after dropout divided by design effect) is equal to 55 per school.

With the given sample size and assuming a significance level (α) of .05 and a power of 80%, we can demonstrate a Cohen *d* of 0.54, which means we can detect a moderate effect size on MVPA [26]. Based on a within-group SD of 20.38 [27], a difference in mean absolute MVPA of 11 min/day between the intervention and control groups can be detected.

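### The planned baseline significance tests treat children as independent although schools are randomized; for a variable clustered like MVPA, a nominal 5% test would reject in about 32% to 46% of null cases.

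*Protocol article*

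**What the plan says.** The design is clustered: "The BOOSTH study is a cluster randomized controlled trial at 16 primary schools located in the province of Limburg". Under Recruitment and Participants, schools are allocated to the two conditions, stratified by community and school size. Sample Size Requirements adds: "Children are nested within schools, with eight intervention and eight control schools". It expects 60 children in each ("it is expected that about 60 children per school will participate"), gives a range for the correlation ("It is assumed that the intraclass correlation coefficient is between 0.05 and 0.10") and concludes that, at 0.10, "the design effect (accounting for clustering of 60 children within a school) is equal to 6.9".

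The Statistical Analysis Plan section then fixes two analyses that treat clustering differently:

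- Baseline comparison: "Baseline characteristics will be analyzed for differences between the groups, using independent sample". The sentence goes on to name the t test, with Mann-Whitney U as the alternative, for numerical variables; categorical variables get a chi-square or Fisher exact test. No adjustment for school is mentioned.
- Effects on numerical outcomes: "will be analyzed using linear mixed models in order to correct for dependent observations owing to repeated measurements within a child and clustering of children". The model carries a random intercept at school level.

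The same section sets the significance threshold at P<.05.

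**The concern.** The baseline tests take their standard errors from the number of children, but chance imbalance between the arms arises mainly from which 8 of the 16 schools fall in each arm. When children in the same school resemble each other, the arm means vary more than those standard errors allow, and p-values come out too small. The article recognizes this for the outcomes and for the sample size, but not for the baseline comparison. Baseline MVPA would thus be tested as independent data in the baseline table and modelled as clustered data in the effect analysis.

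At stake is how the baseline table is read. The study collects many baseline variables: activity, anthropometrics, blood pressure, retinal vessels, aerobic performance, quality of life, motivation and parenting. For those that cluster by school, differences flagged as significant could make a sound allocation look faulty. Nor could such tests serve the one useful purpose they might have in a cluster trial, which is to look for differential recruitment of children between arms.

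**Working it through.** **Inputs (Sample Size Requirements, unless noted).** 8 schools per arm; m = 60 children per school, so 480 per arm; intraclass correlation (ICC) 0.05 to 0.10; threshold .05 (Statistical Analysis Plan). Two-sided testing is assumed, since sidedness is not stated. The 20% dropout does not apply at baseline.

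**The plan's own figures.** Design effect DE = 1 + (m − 1) × ICC.

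- At ICC 0.10: 1 + 59 × 0.10 = 6.9, as stated.
- Effective sample size after dropout: 480 × 0.8 / 6.9 = 55.65 per arm. The stated value of 55 is reproduced as a figure per arm.
- Detectable difference at n = 55 per arm and 80% power: d = 0.534 (normal) or 0.539 (t), against the stated 0.54; 0.54 × 20.38 = 11.0 min/day.

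The article's calculation is therefore reproduced, and the same design effect can be applied to the baseline tests.

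**False-positive rate of a test that ignores school.** The true variance of the difference in arm means is DE times the variance the test assumes. The standard error is thus too small by a factor √DE, and the actual two-sided rate is 2 × (1 − Φ(1.96 / √DE)).

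| ICC | DE | √DE | 1.96 / √DE | Actual rate |
|---|---|---|---|---|
| 0 | 1.00 | 1.00 | 1.96 | 5% |
| 0.01 (outside the stated range) | 1.59 | 1.26 | 1.55 | 12.0% |
| 0.05 | 3.95 | 1.99 | 0.99 | 32.4% |
| 0.10 | 6.90 | 2.63 | 0.75 | 45.6% |

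**Check by simulation.** 8 versus 8 schools of 60 children, no true difference; 10,000 runs for the t test and 3,000 for the others.

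| ICC | t | Mann-Whitney | Chi-square | Fisher |
|---|---|---|---|---|
| 0 | 4.9% | 5.0% | 4.9% | 4.0% |
| 0.05 | 32.2% | 31.4% | 31.4% | 30.0% |
| 0.10 | 45.6% | 45.6% | 46.9% | 45.1% |

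All four planned tests are affected alike. With no clustering the rates return to 4% to 5%, so clustering is the cause.

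**Effect of stratification.** The article does not say how much between-school variance the strata explain, so the share s is an assumption. If the strata are balanced across arms, only (1 − s) of the between-school variance contributes to chance imbalance, and DE is replaced by m × ICC × (1 − s) + (1 − ICC).

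| ICC | s = 0 | s = 25% | s = 50% |
|---|---|---|---|
| 0.05 | 3.95, 32% | 60 × 0.05 × 0.75 + 0.95 = 3.20, 27% | 60 × 0.05 × 0.50 + 0.95 = 2.45, 21% |
| 0.10 | 6.90, 46% | 60 × 0.10 × 0.75 + 0.90 = 5.40, 40% | 60 × 0.10 × 0.50 + 0.90 = 3.90, 32% |

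The rate falls, but stays well above 5% over this range.

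**The case against.** The strongest reply is that little depends on these tests. Several parts of it stand.

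- **The primary analysis.** A reader might infer that false baseline signals will shape the primary model. The text does not support this. Covariates are the stratification variables and variables related to outcome or missingness, with BMI z-score, sex, age and parenting style named as examples. Baseline p-values are nowhere given as a criterion, and the outcome model carries a random school intercept.
- **Reach of the percentages.** The ICC range is assumed in the calculation for MVPA, and the article gives none for any other baseline variable. It is tempting to expect spurious findings throughout the table. For variables with little school clustering, which may include sex, the rate would be near 5%.
- **Stratification.** The 32% to 46% range takes no credit for it, so it is not a prediction for this trial.
- **Whether testing has any use.** A reader might argue that baseline tests are pointless because every difference must be due to chance. That holds for the allocation of schools. Children, however, enter by individual consent, and the article does not say whether consent preceded allocation. If it came afterwards, differential participation could produce differences that are not due to chance, and a baseline comparison would have a purpose.

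None of this rescues the tests as written. They ignore a dependence that the same section corrects for elsewhere. A purpose such as detecting differential recruitment calls for a test with a correct error rate.

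**Conclusion.** The point holds, with limited consequence. The baseline tests are specified in a way that conflicts with the trial's own design assumptions, and their p-values will be too small for any characteristic that clusters by school. This is a stated choice of method, not a detail left to a fuller document.

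The size is about 32% (ICC 0.05) to 46% (ICC 0.10) false positives at a nominal 5%. This assumes MVPA-like clustering, 60 children in every school, two-sided tests and no gain from stratification. It falls to about 21% to 32% if the strata explained half of the between-school variance.

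The damage is confined to misleading statements about baseline imbalance. The article gives no ground for concluding that the primary test is biased or that covariate selection depends on these tests.

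**What to change.** Replace the sentence on baseline testing with a descriptive comparison: means and SDs, medians and IQRs, or counts and percentages by arm, at child and school level, for example with standardized differences. If a test is kept for a stated purpose, such as looking for differential recruitment, it should account for school, either through a random school effect (as already planned for the outcomes) or by analysing the 16 school-level summaries. With 8 schools per arm, a two-sample comparison of school means has 14 degrees of freedom and a false-positive rate of about 5%.

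The cost is a change of wording. No extra data are needed, and the descriptive option means less analysis work.

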### Measurements

#### Data Collection

As shown in Figure 1, study measurements will be performed at baseline (T0) and after 3 months (T3), 6 months (T6), and 12 months (T12). A trained research team will perform the measurements during school hours at the primary schools. The research team will be instructed to complete the questionnaires together with the children. Stratified intervention and control schools will be measured within the same week to prevent confounding effects of, for example, different seasons and weather-dependent factors influencing PA. Measurements will be performed using a standardized protocol.

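### With only a time-constant school intercept in the mixed model, any change, group-by-time or baseline-constrained 12-month test of BOOSTH would be anti-conservative if school means drift separately

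*Protocol article*

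**What the plan says.** The Statistical Analysis Plan section of the protocol article uses linear mixed models for MVPA and the other numerical outcomes, "in order to correct for dependent observations owing to repeated measurements within a child and clustering of children within a school". It then fixes the structure: "A random intercept on school level and an unstructured covariance structure for repeated measures will be included". No school term that varies over time is named.

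Under Sample Size Requirements, the target is "to detect a difference in MVPA between the intervention and control groups after 12 months". That section also gives the design: "Children are nested within schools, with eight intervention and eight control schools", and "it is expected that about 60 children per school will participate". On clustering it says: "It is assumed that the intraclass correlation coefficient is between 0.05 and 0.10".

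Under Data Collection, children are measured at baseline and at 3, 6 and 12 months. Stratified intervention and control schools are measured in the same week "to prevent confounding effects of, for example, different seasons and weather-dependent factors influencing PA".

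**The concern.** The model gives the child level full freedom over time and gives the school level none. A constant school intercept accounts for schools that are persistently more or less active. It does not account for a school whose mean MVPA moves between visits for reasons of its own, such as a change of teacher, PE programme or local event.

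In a T12-minus-T0 contrast the constant intercept subtracts out. The model's standard error for that contrast then contains child-level variance divided by the number of children, and almost nothing for variation between schools. Real school-specific drift is spread over hundreds of children, when it should be averaged over eight schools per arm.

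The standard error would be too small, and ordinary school fluctuation could be read as an effect of BOOSTH. Because the same model serves all numerical outcomes, the problem would not be confined to MVPA.

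**Working it through.** **Inputs from the article (Sample Size Requirements).** 8 schools per arm; 60 children per school; dropout 20%, so 60 × 0.8 = 48 children per school; ICC 0.05 to 0.10; alpha 0.05; power 80%; SD 20.38 min/day.

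**Assumptions, because the article gives no value.** Within-child correlation between visits ρ = 0.5. Autocorrelation of school effects between visits (*a*), shown from 1.0 to 0.5. Two-sided testing.

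**The article's own figures reproduce.**
- Design effect: 1 + 59 × 0.10 = 6.9.
- Effective size: 480 × 0.8 / 6.9 = 55.7. This is per arm; the article labels it per school, where it would be about 7. The detectable effect uses the per-arm figure and is not affected.
- Detectable *d*: (1.96 + 0.84) × √(2/55.7) = 0.53. The *t*-test version with 55 per arm gives 0.54, as stated.
- 0.54 × 20.38 = 11.0 min/day, as stated.

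This calculation charges the full clustering penalty. The question is whether the fitted model charges it too.

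**Size of the T12-minus-T0 group contrast.** Take total variance as 1 and let *m* = 48. Dropping the common factor, each school's mean change has:
- true variance: ICC(1 − *a*) + (1 − ICC)(1 − ρ)/*m*
- variance the planned model credits: about (1 − ICC)(1 − ρ)/*m*, because the constant intercept cancels
- size of the nominal 5% test: 2 × [1 − Φ(1.96 × √(model/true))]

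Worked case, ICC 0.10 and *a* = 0.8:
- school part: 0.10 × 0.2 = 0.0200
- child part: 0.90 × 0.5 / 48 = 0.0094
- true: 0.0294; model: 0.0094
- standard-error ratio: √(0.0294/0.0094) = 1.77; size 26.8%

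If the drift is absorbed into the child residual, the model variance is (0.02 + 0.45)/48 = 0.0098, the ratio is 1.73 and the size is 26%. The conclusion does not change.

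| *a* | Analytic size, ICC 0.05 | Analytic size, ICC 0.10 |
|---|---|---|
| 1.0 | 5.0% | 5.0% |
| 0.95 | 8.0% | 11.3% |
| 0.9 | 11.0% | 17.3% |
| 0.8 | 16.7% | 26.8% |
| 0.5 | 29.7% | 43.6% |

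At *a* = 0.8 to 0.9, letting ρ run from 0.3 to 0.7 widens the range to about 9 to 36%.

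**Simulation.** The planned model was fitted by REML to 500 simulated null trials per scenario (8 + 8 schools, 48 children each, four visits, complete data, ρ = 0.5). The Monte Carlo standard error is √(*p*(1 − *p*)/500), about 1 point at 5% and 2 points at 25%. Each cell gives ICC 0.05 / ICC 0.10.

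| Contrast | *a* = 1.0 | 0.9 | 0.8 | 0.5 |
|---|---|---|---|---|
| Change to T12, normal reference | 7% / 4% | 12% / 15% | 16% / 25% | 31% / 45% |
| Joint group-by-time, 3 df | 7% / 5% | 17% / 25% | 27% / 45% | 54% / 73% |
| Baseline-constrained T12, *t* on 14 df | 4% / 3% | 8% / 13% | 12% / 20% | 26% / 38% |
| Unadjusted T12 difference, *t* on 14 df | 4% / 5% | 5% / 5% | 4% / 4% | 9% / 10% |
| Change, school means free by visit, *t* on 14 df | 6% / 4% | 6% / 5% | 6% / 5% | 6% / 7% |

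The unadjusted 12-month difference holds because the school intercept stays in its standard error. The last row shows that the excess disappears once school means may vary by visit. The third row, which already uses 14 degrees of freedom, shows that small-sample degrees of freedom alone do not repair a missing variance component.

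**The case against.** The strongest reply is that the article never says a group-by-time effect will be tested. Its one stated comparison is the group difference after 12 months. The sample size is built on absolute MVPA with the full ICC and no baseline correlation. Read that way, the planned model is close to valid. This stands: a reader might infer that the primary test is a group-by-time test and is therefore invalid, and the document does not support that. Nor is the unnamed contrast or degrees-of-freedom method a fault in itself, since an article may leave both to a fuller plan. For the same reason, the article cannot be said to use child-level degrees of freedom.

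Second, the inflation depends on an autocorrelation that the article does not give. A reader might take 10 to 25% as the trial's false-positive rate. It is only part of a range that starts at 5%.

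Third, randomization is stratified by community, and stratified schools are measured in the same week. Drift from season, weather or shared local conditions therefore tends to cancel between arms. This also stands in part. Drift peculiar to one school remains, and the autocorrelation above should be read as applying to that remainder.

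What the reply does not remove is that the covariance structure is a stated choice, not an omitted detail. Change, interaction and baseline-constrained effects are all natural uses of a four-visit model that includes baseline, and the structure is unsafe for each of them.

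**Conclusion.** The point holds conditionally. If the effect is taken from a change, group-by-time or baseline-constrained contrast, and school means do not move exactly in parallel within an arm, the stated model understates the standard error. With 48 children per school, ρ = 0.5, ICC 0.05 to 0.10 and autocorrelation 0.8 to 0.9, a nominal 5% change test has true size of about 11 to 27% (12 to 25% simulated), and a baseline-constrained 12-month effect about 8 to 20%. There is no inflation at autocorrelation 1.0; at 0.5 the change test reaches 30 to 44%. An unadjusted 12-month difference on school-level degrees of freedom is little affected at 0.8 or higher. The algebra is certain. The size in this trial is not, because it depends on a quantity the article does not report.

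**What to change.** - Add a random school-by-visit effect to the random school intercept, or otherwise let school means vary by visit. Keep the unstructured child-level covariance.
- Use small-sample degrees of freedom (Satterthwaite, or school-level with 16 − 2 = 14).
- State the 12-month group contrast as the primary test and say how baseline enters it.
- Check the result with a baseline-adjusted analysis of school means, 8 versus 8.

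The cost is one model term and a sentence or two in the plan, somewhat wider confidence intervals, and one more variance component to estimate from 16 schools. If the school-by-visit variance is zero, the model reduces to the planned one. The simulated correction used an unstructured school-level covariance on 14 degrees of freedom. The school-by-visit model with Satterthwaite degrees of freedom was not itself simulated, which is a further reason to keep the school-level check.
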